#### Ethics and registration

Ethical approval for this research has been granted from University of East London (UEL) Research Ethics Committee on 13 August 2020 (ID: ETH2021-0006) and from Manchester University Research Ethics committee on 8 September 2020 (UEL approval accepted in lieu of separate institutional approval). Ethical approval involved producing a Data Management Plan which outlines details and procedures for maintaining participant details confidential, and for secure storage and disposal of study data. The trial design process has been methodical, involving iterative stages of development and peer review commentary feedback and, as a result, no protocol modifications are anticipated. However, should protocol amendments be required, institutional ethical amendments will be submitted promptly, and associated trial documentation amended as required in all locations.

### Plans to promote participant retention and complete follow-up {18b}

Not applicable as plans to promote participant retention and complete follow-up will not be included in this trial.

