### Sample size {14}

#### Statistical power and sample size

An a priori power analysis has been conducted using G*Power V.3.1 for an ANCOVA model estimating fixed effects, main effects and interactions [44]. A medium effect size (*f*=0.25) with power set to 0.80 and alpha set to 0.01 (adjusted given multiple tests and therefore to control for type I error rate inflation) will be sought. Inclusion of six covariates (gender; age; ethnicity; occupation; approximate time spent in places where wearing face coverings would be mandatory; imagery ability) was specified. Power analysis indicated that a minimum sample size of 254 will be required. In developing the recruitment strategy, it is important to be mindful of introducing attrition bias, i.e. bias created by retaining participants with particular characteristics in a way that alters the complexion of the sample. Guidance on acceptable attrition levels has indicated that > 20% study attrition increases the risk of attrition causing serious threats to study validity [45] though debate surrounds precisely when attrition bias may most threaten study validity (e.g. [46, 47]). The study aim is, therefore, to recruit 312 individuals at baseline/T1 to meet a required sample size of 260 at follow-up/T3 (i.e. allowing for no more than 20% attrition).

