### Recruitment {15}

#### Enrolment

Details of the schedule of enrolment, interventions, and assessments are shown diagrammatically in Fig. 1.

As described above; all measures will be acquired via Qualtrics, an online platform which will host our study questionnaire. A URL link to the Qualtrics hosted survey will be embedded into an email message promoting the study and this promotional message will be sent out in an email circular message to prospective participants (staff and students at UEL and Manchester University). We will follow bi-weekly enrolment drives to maximize the possibility of an even spread of responses throughout the study recruitment phase, and to maintain a consistent promotional presence of the recruitment message. We will aim to complete all study enrolment within six months: recruitment will start in approximately mid-September 2020 and we will aim to complete all study enrolment (i.e. responses at T1, T2 and T3) by late February 2021. Where enrolment continues for longer than 6 months, we will explore ‘date of participant response’ as a covariate in main intervention study analyses. We will supplement our university-focused recruitment approach by also posting a URL link to the Qualtrics-hosted survey twice each week on social media (e.g. on Twitter, via Facebook posts). Participant recruitment will be led by the protocol author (the UEL-based study researcher) and will be supplemented by recruitment activities led by a second researcher based at Manchester University.

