## Data collection and management

### Plans for assessment and collection of outcomes {18a}

#### Data collection and management

Participant names will not be included in the dataset and each participant will be assigned a study ID. All data will be downloaded in secure form to institutional cloud services (i.e. OneDrive). All data will be backed-up securely and all data files will be securely password protected and encrypted. Throughout project activities, data files and printed materials that are no longer required will be destroyed. Email address data will be stored in a separate document in an encrypted folder and will be destroyed once recruitment is completed. Range and consistency checks will be conducted on all questionnaire data promptly by the research team. Because questionnaire data will be collected using a ‘Force Response’ setting on Qualtrics there will be no missing data for this study. To address incomplete participant responses we will conduct an intention-to-treat (ITT) analysis in addition to the complete case analysis. ITT is an assessment of all trial participants in analysis regardless of whether or not they provided incomplete responses or failed to provide follow-up responses and provides a way of producing an unbiased estimate of intervention efficacy of the intervention in respect of study adherence [48].

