## Trial status

Enrolment for this study began on 19 August 2020 and ended on 28 February 2021. The total number of participants recruited includes a sample with complete data at T1/T2 only (*n* = 465) and a sample with complete data at T1 and T3 (*n* = 297). This study protocol is Version 2.0, dated 9 September 2020.

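### The protocol rules out any retention effort although its primary outcome depends on a remote 1-month return and it treats attrition above 20% as a threat to validity; the trigger for destroying email addresses is also ambiguous

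*Protocol article*

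**What the plan says.** Item {18b} of the protocol article is explicit: "Not applicable as plans to promote participant retention and complete follow-up will not be included in this trial". This is a stated choice and not a detail left to another document.

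The sample size section (item {14}) cites guidance that "> 20% study attrition increases the risk of attrition causing serious threats to study validity", and plans accordingly to "recruit 312 individuals at baseline/T1 to meet a required sample size of 260 at follow-up/T3 (i.e. allowing for no more than 20% attrition").

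Under Data collection and management (item {18a}): "Email address data will be stored in a separate document in an encrypted folder and will be destroyed once recruitment is completed". Email is the only contact detail that the article mentions holding.

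The Enrolment text (item {15}) says "we will aim to complete all study enrolment (i.e. responses at T1, T2 and T3) by late February 2021", so there the completion of enrolment includes T3.

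Outcomes {12} and the Behavioural measure text say that face covering behaviour is recorded at T1 and T3 only, with T3 at 1 month as the primary time point. Trial status reports 465 people with complete data at T1/T2 only, and "a sample with complete data at T1 and T3" of 297.

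**The concern.** Behaviour is not measured at T2, so a participant who does not return at T3 contributes nothing observed after baseline to the primary comparison. The additional intention-to-treat analysis under item {18a} cannot recover an observation that was never made. Preventing loss is therefore the main protection, and item {18b} declines it.

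What is at stake is bias. Participants are remote, contact is online, and the burden before T3 differs by arm: one image in the control arm, an estimated 8–12 minutes for a single imagery exercise and 15–25 minutes for the combined arm. Return could plausibly depend on arm and on motivation, and motivation is likely to be related to wearing a face covering. This is the selective retention that item {14} itself warns of.

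The destruction of addresses adds a second, conditional risk. Deletion cannot be undone, so its trigger needs one meaning.

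**Working it through.** **1. The plan's own sample size.** Inputs from item {14}: f = 0.25, alpha = 0.01, power = 0.80, six covariates; four groups from item {16a}. Noncentral F for a fixed-effects ANCOVA, with λ = N·f², df1 = 3 and df2 = N − 4 − 6, gives N = 254 (power 0.802). The stated minimum of 254 is reproduced.

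**2. How much loss the plan tolerates.**
- 312 to 260: 1 − 260/312 = 16.7%, or 52 people.
- 312 to 254: 1 − 254/312 = 18.6%.
- At exactly 20% loss: 312 × 0.80 = 249.6, power about 0.79.

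The 312 is 260 × 1.2; retaining 260 after 20% loss needs 260/0.80 = 325. That is a separate matter, but it means the working margin is narrower than the stated limit, which makes retention matter more.

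**3. Address destruction, two readings.** T3 is taken at 1 month, as in Objectives {7} and Outcomes {12}; the Design subsection says 1 week, which would make the first figure smaller.

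| Meaning of completed recruitment | Support in the protocol | People who could not be emailed for T3 |
|---|---|---|
| End of T1 entry | Item {14} uses the verb recruit for baseline entry | About 312/6 = 52 (16.7%), assuming even entry over the planned six months |
| End of T1, T2 and T3 responses | Item {15} counts T3 responses within completed enrolment | 0 |

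On the first reading the 52 equal the whole 312-to-260 margin, before any voluntary drop-out.

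**4. Reported counts (Trial status).**
- If the 297 are a subset of the 465: (465 − 297)/465 = 168/465 = 36.1% without T3.
- If the two samples are separate: 465/(465 + 297) = 465/762 = 61.0%.

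Both exceed 20%.

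**5. Bias or numbers?** 297 exceeds both 254 and 260, and the calculation in step 1 gives power of about 0.88 at N = 297. The size target was met because more people were recruited than planned. Bias is different. If a fraction L of an arm is lost and those retained score d higher on average than those lost, the observed arm mean is too high by L·d: 0.20·d at the plan's limit and 0.361·d at 36.1%. The arm comparison is unaffected only if L·d is equal across arms. Extra recruitment does not change this. The documents give neither d nor L by arm, so the bias cannot be quantified.

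**The case against.** The strongest objection concerns the addresses. A reader might infer that the protocol deletes them before late entrants reach T3. The text does not establish this. Item {15} sits under a recruitment heading and counts T3 responses within completed enrolment, with a target of late February 2021 that matches the reported end date of 28 February 2021. A separate Data Management Plan, mentioned under Ethics and registration but not shown, may settle the date. This objection stands: the wording is ambiguous, and the figure of 52 belongs to one reading only.

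A reader might also infer that the trial could not stay within 20%. That does not follow. Having no retention plan raises the risk of loss but does not make 20% or less impossible, and the protocol gives no expected return rate with or without reminders. Nor does item {18b} mean that no T3 link was sent; holding email addresses suggests some follow-up contact.

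Thirdly, the reported counts do not prove the mechanism. The relation between the two samples is unclear, and participants can also be excluded for inattentive responses or poor engagement with the exercise. Trial status does not say whether its counts precede those exclusions, so 36.1% may not be pure drop-out. Nothing links it to absent reminders or deleted addresses. This also stands.

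Finally, unequal loss by arm is plausible but not shown. The exercise is finished about a month before T3, and its effect on later return is unknown.

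None of this removes the conflict between items {14} and {18b}.

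**Conclusion.** The point holds in a limited form. The protocol names attrition above 20% as a serious threat, rests its primary outcome on a remote return at 1 month, and states that nothing will be done to promote that return. This is a weak design choice with a cheap alternative.

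The deletion trigger is ambiguous. Between 0 and about 52 people (16.7% of 312) could be out of email reach at T3, depending on the reading; the upper figure assumes even entry over six months, a 1-month T3 and email as the only contact route.

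The reported loss of 36.1% assumes that the 297 are a subset of the 465. It is consistent with the limit having been exceeded, but it identifies no cause. The concern is possible attrition bias in the primary comparison, of unknown size and direction; it is not a failure to reach the planned sample size.

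**What to change.** 1. Replace item {18b} with an automated T3 invitation and a small, fixed number of survey-platform reminders to non-responders, identical in all arms and within a fixed window. Two or three reminders over 14 days would be one example; the protocol gives no basis for particular values, so the sponsor should choose them and state them in advance.
2. In item {18a}, tie destruction of addresses to the close of the last participant's T3 window, and make the Data Management Plan agree.
3. Report T3 return by arm, set against the 20% limit.

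This is a cheap improvement. It needs survey-platform emails and a short wording change. The downside is that addresses are held a few weeks longer and non-responders receive some extra emails.

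Trial status says that enrolment has ended, so reminders can no longer help this cohort. For this trial, the protocol update promised under item {31c} should state what follow-up contact was made, when the addresses were destroyed, and whether the 297 are a subset of the 465. Step 3 still applies in full.

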### Data management {19}

Details are provided in the ‘Plans for assessment and collection of outcomes {18a}’ section above.

### Confidentiality {27}

Details are provided in the ‘Plans for assessment and collection of outcomes {18a} section above.

### Plans for collection, laboratory evaluation and storage of biological specimens for genetic or molecular analysis in this trial/future use {33}

Not applicable as no biological specimens will not be collected as part of this trial.

## Statistical methods

### Statistical methods for primary and secondary outcomes {20a}

#### Planned statistical analyses

Across T1–T3, Mean/SD values will be reported for behaviour and the psychological variables and percentages (of total sample) will be reported for demographic variables. Hypotheses stated previously will be tested via a series of ANCOVAs. Intervention condition will be a between-participants variable (outcome, process, combined, control) and time will be a within-participants variable (T1, T2, T3). The primary outcome (face covering behaviour) and secondary outcomes (intention, attitude, subjective norms, PBC, barrier self-efficacy) will be assessed as separate dependent variables. A factorial superiority framework will be adopted for this trial. This approach is preferred to a parallel group trial because it will permit testing for superiority of assignment to a specific imagery exercise technique (e.g. outcome imagery), regardless of study condition, rather than comparing simple assignment to one of the four conditions. Consistent with previous mental imagery interventions, demographic variables will be included as covariates. Where statistically significant effects are demonstrated from ANCOVA analyses, simple effects analyses will be conducted from which estimated marginal means will be reported for all primary and secondary outcome variables. The alpha level will be set at 0.01 for all analyses to control for Type I error rates. Moderation effects of personality traits (conscientiousness, narcissism, Faith in humanity, Kantianism, Humanism) on study intervention effects will be assessed using the PROCESS software macros (V.3.4) on IBM SPSS (V.26).

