##### Hypotheses

It is hypothesized that individuals assigned to any imagery intervention condition will report, at T2 and T3:

*H1*. Significantly higher levels of T2 behaviour (i.e. self-reported face covering adherence) relative to the control condition.

*H2*. Significantly higher intentions to wear face coverings in public places where these are required, relative to the control condition.

*H3*. Significantly more favourable attitudes, subjective norms, barrier self-efficacy and perceived behavioural control linked to face covering wearing relative to control condition participants.

*H4*. Finally, that imagery intervention effects will be conditional on being more conscientious, less narcissistic, and being characterized by higher levels of light triad personality traits.

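### The flat 0.01 level is said to be already adjusted for multiple testing, but it covers only five tests, and H2 to H4 involve between 10 and about 45

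*Protocol article*

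**What the plan says.** Two places in the protocol article fix the significance level and give a reason for it. Under Planned statistical analyses ({20a}): "The alpha level will be set at 0.01 for all analyses to control for Type I error rates". Under Statistical power and sample size ({14}) the calculation is run "with power set to 0.80 and alpha set to 0.01 (adjusted given multiple tests and therefore to control for type I error rate inflation". The two agree on the level. Neither says how many tests it was adjusted for, or which ones.

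The tests come from several sections:

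- Outcomes {12} names one primary outcome, behaviour at T3, and five secondary outcomes (intention, attitude, subjective norms, perceived behavioural control, barrier self-efficacy) at T2 and T3. {20a} analyses each as its own dependent variable.
- Hypotheses states H2 for intention. H3 covers the other four constructs: "Significantly more favourable attitudes, subjective norms, barrier self-efficacy and perceived behavioural control linked to face covering wearing relative to control condition participants". Both are introduced as holding at T2 and T3.
- H4 says that "imagery intervention effects will be conditional on being more conscientious, less narcissistic, and being characterized by higher levels of light triad personality traits", and {20a} lists five traits: "Moderation effects of personality traits (conscientiousness, narcissism, Faith in humanity, Kantianism, Humanism) on study intervention effects will be assessed".
- Design gives a 2 × 2 structure over time, and {20a} adopts a factorial framework so that each imagery technique can be tested across conditions. {20a} also describes condition as a single four-level variable.

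**The concern.** The article presents 0.01 as a finished multiplicity adjustment. That is a statement about the error properties of the design, and it can be checked against the tests the article itself plans. A level of 0.01 is what Bonferroni gives for 5% shared over five tests, and the tests for H2 to H4 outnumber five.

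This matters because the secondary results are meant to carry conclusions. The Background accepts change in social cognitions as a way to assess an intervention. The Discussion makes it the trial's secondary purpose and hopes to learn about motivational pathways. H3 has four constructs at two time points and H4 has five traits, and the article does not say whether one significant component or all of them would count as support. If one is enough, a single chance result could be reported as support under a level that readers are told already allows for multiple testing.

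**Working it through.** **Step 1. Reproduce the plan's own figure.** Inputs from {14}: f = 0.25, power 0.80, alpha 0.01, six covariates, and four groups from the design. For an ANCOVA F test the noncentrality is f²N and the denominator df is N − groups − covariates. With N = 254 these are 0.0625 × 254 = 15.875 and 254 − 4 − 6 = 244. With numerator df = 3 the power is 0.802, and 254 is the smallest N that reaches 0.80. Numerator df of 1, 2 and 6 give 191, 227 and 311. So 254 is correct for one three-degree-of-freedom comparison of the four conditions at 0.01.

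**Step 2. What 0.01 covers.** For m independent tests with all nulls true, the chance of at least one false positive is 1 − 0.99^m. For m = 5 this is 4.9%, and 0.05/5 = 0.01.

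**Step 3. Count the tests for H2 to H4.** The text allows several readings:

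- A: one omnibus test per secondary outcome and one per trait, 5 + 5 = 10.
- B: one any-imagery contrast per secondary outcome at T2 and at T3, plus the traits, 5 × 2 + 5 = 15.
- C: two factorial main effects, 5 × 2 × 2 + 5 × 2 = 30.
- D: two main effects and their interaction, 5 × 2 × 3 + 5 × 3 = 45.

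The interaction in D has a basis in the text: {6b} includes the combined arm partly to look for synergy.

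**Step 4. Family-wise error, all nulls true.**

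| Reading | m | Independent, 1 − 0.99^m | Correlated (simulated) | Hypothesised direction only, 1 − 0.995^m | 0.05/m |
|---|---|---|---|---|---|
| A | 10 | 9.6% | not simulated | 4.9% | 0.005 |
| B | 15 | 14.0% | 10.1–13.1% | 7.2% | 0.0033 |
| C | 30 | 26.0% | 19.3–24.3% | 14.0% | 0.00167 |
| D | 45 | 36.4% | 27.4–34.3% | 20.2% | 0.0011 |

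The correlated column rests on assumed correlations, since the article gives none: 0.3 to 0.7 between outcomes, 0.5 to 0.8 between time points and 0.2 between trait tests (400,000 draws, two-sided 0.01). The direction-only column assumes independent tests, with half of each 0.01 in the favourable tail. For reading A that halving is only nominal, because an omnibus F test on three degrees of freedom has no direction.

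**Step 5. Primary outcome.** One, two or three tests of T3 behaviour at 0.01 give 1.0%, 2.0% and 3.0%, all below 5%. Adding one omnibus behaviour test to reading A, so that H1 to H4 are all covered, gives 1 − 0.99^11 = 10.5%.

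These counts leave out mediation, moderation by imagery ability, follow-up simple effects and the parallel intention-to-treat and complete-case analyses.

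**The case against.** The strongest defence is that 0.01 may have been chosen for the five secondary outcomes. {20a} allows condition to be one four-level variable with time as a factor in the same model, and Step 1 shows that the sample size was built on one omnibus test. On that reading the five secondary outcomes give 4.9%, which is what 0.01 protects. All six outcomes give 1 − 0.99^6 = 5.9%. This is a coherent reading, but the article does not state it, and it leaves out H4. Adding the five trait tests to the secondary outcomes brings the figure to 9.6%.

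A reader might also infer more than the documents support:

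- **That there is no correction and no hierarchy.** {14} makes 0.01 itself the correction. One primary outcome is named, the goals are divided into primary and secondary, and simple effects follow only a significant ANCOVA effect. What is absent is any order or family within H2 to H4.
- **That H2 to H4 are confirmatory claims on a par with H1.** The article does not use that word. The abstract calls the traits putative moderators, and the Objectives speak of examining them.
- **That a false claim of support has a single known chance of 20% to 30%.** That range fits the factorial counts only. The count is ambiguous, and because the hypotheses are directional, errors in the favourable direction are about half as frequent.
- **That a promised 1% family-wise rate is exceeded many times over.** No such rate is promised; 0.01 is the level for each analysis.

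Finally, test ordering and the rule for declaring H3 supported are details that an analysis plan not shown here may supply, so their absence alone is no fault. What remains is the article's own statement that 0.01 has already dealt with multiple testing.

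**Conclusion.** The concern holds in a limited form. The statement that 0.01 is adjusted for multiple tests and controls Type I error is not true of H2 to H4 taken together. The level covers five tests, the family is undefined, and the planned tests number from 10 to about 45. The two-sided family-wise error is about 10% to 36% if tests are independent. It is lower under correlation: about 10% to 34% across the 15-, 30- and 45-test readings under the assumed values. If only errors in the hypothesised direction count, the range is about 5% to 20%. All these figures assume that every null hypothesis is true.

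The primary outcome is at 1% to 3% and N = 254 reproduces, so the main conclusion of the trial is not threatened. The weakness is in how much trust the secondary and moderator findings can bear. It should be corrected, but it does not undermine the design.

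**What to change.** - In {14} and {20a}, limit the statement that 0.01 controls Type I error to the primary test of T3 behaviour.
- For H2 and H3, define the family as the five constructs × T2 and T3 × the factorial effects on which a claim will be made. Apply Holm at a stated 5% family-wise level. With one, two or three effects the family is 10, 20 or 30 tests, so the smallest p-value is compared with 0.005, 0.0025 or 0.00167.
- Report H3 construct by construct, so that no single result stands for the whole hypothesis.
- Label the five H4 trait moderations as exploratory, and give interaction estimates with confidence intervals.

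Testing H2 and H3 only if H1 succeeds is not required. The Background and Objectives treat change in cognitions as a goal of its own, assessed from T2 onwards, so gating would be a debatable trade-off.

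The cost is wording in two sections and a few lines of analysis syntax. No new data are needed, and N and the primary test are unchanged. Some secondary and moderator results become harder to claim. Trial status reports that enrolment has ended, so the change affects only analysis and reporting. If outcome data have already been examined, the report should say when the rule was adopted.
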